## Abstract

**Background:**

There is an ongoing debate whether electronic cigarettes (e-cigarettes) should be advocated for smoking cessation. Because of this uncertainty, information about the use of e-cigarettes for smoking cessation is usually not provided in governmental smoking cessation communications. However, there is an information need among smokers because despite this uncertainty, e-cigarettes are used by many smokers to reduce and quit tobacco smoking.

**Objective:**

The aim of this study is to describe the protocol of a randomized controlled trial that assesses the effect of providing tailored information about e-cigarettes compared to not providing this information on determinants of decision making and smoking reduction and abstinence. This information is provided in the context of a digital smoking cessation intervention.

**Methods:**

A randomized controlled trial with a 6-month follow-up period will be conducted among adult smokers motivated to quit smoking within 5 years. Participants will be 1:1 randomized into either the intervention condition or control condition. In this trial, which is grounded on the I-Change model, participants in both conditions will receive tailored feedback on attitude, social influence, preparatory plans, self-efficacy, and coping plans. Information on 6 clusters of smoking cessation methods (face-to-face counselling, eHealth interventions, telephone counselling, group-based programs, nicotine replacement therapy, and prescription medication) will be provided in both conditions. Smokers in the intervention condition will also receive detailed tailored information on e-cigarettes, while smokers in the control condition will not receive this information. The primary outcome measure will be the number of tobacco cigarettes smoked in the past 7 days. Secondary outcome measures will include 7-day point prevalence tobacco abstinence, 7-day point prevalence e-cigarette abstinence, and determinants of decision making (ie, knowledge and attitude regarding e-cigarettes). All outcomes will be self-assessed through web-based questionnaires.

**Results:**

This project is supported by a research grant of the National Institute for Public Health and the Environment (Rijksinstituut voor Volksgezondheid en Milieu). Ethical approval was granted by the Ethics Review Committee Health, Medicine and Life Sciences at Maastricht University (FHML-REC/2019/072). Recruitment began in March 2020 and was completed by July 2020. We enrolled 492 smokers in this study. The results are expected to be published in June 2021.

**Conclusions:**

The experimental design of this study allows conclusions to be formed regarding the effects of tailored information about e-cigarettes on decision making and smoking behavior. Our findings can inform the development of future smoking cessation interventions.

**Trial Registration:**

Dutch Trial Register Trial NL8330; https://www.trialregister.nl/trial/8330

**International Registered Report Identifier (IRRID):**

DERR1-10.2196/27088

## Introduction

### Background

Tobacco smoking is a major public health threat, contributing to increased morbidity and mortality [1]. In the Netherlands, tobacco smoking is responsible for more than 19,000 deaths per year [2]. Many smokers report that they want to quit smoking, but only about 4% of smokers trying to quit without assistance succeed in their cessation attempts [3,4]. Most smokers find it hard to quit smoking because of the highly addictive nature of nicotine [5], and while they smoke for the nicotine, their probability of dying prematurely increases owing to the by-products of burnt tobacco (eg, tar) [6]. In this paper, we will describe the study protocol for a randomized controlled trial assessing an intervention aimed at quitting combustible cigarette smoking and the potential added effects of providing tailored information on electronic cigarettes (e-cigarettes).

### e-Cigarettes for Smoking Cessation

e-Cigarettes, also called as electronic nicotine delivery systems, are handheld electronic devices that generate aerosols by heating a liquid that usually contains nicotine, flavorings, and other compounds [7]. Because e-cigarettes do not burn tobacco, users are not exposed to the damaging substances of combustible tobacco [7]. However, it is important to note that, although e-cigarette aerosols generally contain fewer toxic chemicals than cigarette smoke, all tobacco (and related) products, including e-cigarettes, carry risks [8]. Smokers who want to quit smoking can use e-cigarettes as an aid for smoking reduction, cessation, and relapse prevention [7,9]. e-Cigarettes may be advantageous over nicotine replacement therapy because they are able to provide nicotine effectively and mimic the smoking experience [10]. Using e-cigarettes for smoking cessation can be considered as a tobacco harm reduction strategy [11]. There is an ongoing debate whether e-cigarettes should be advocated for smoking cessation [12]. A recent Cochrane systematic review concluded that the current evidence provides moderate certainty that e-cigarettes with nicotine are superior to e-cigarettes without nicotine and nicotine replacement therapy concerning smoking cessation [7]. Reviews on the effectiveness of using e-cigarettes for smoking cessation stress that more evidence is needed to be confident about the effects [7,8,13-15]. Furthermore, e-cigarettes developed quickly in recent years and findings from studies conducted with past generations of e-cigarettes (eg, cigalikes, battery pens) are not applicable to state-of-the-art e-cigarettes (eg, pod mods) [8]. Hence, more randomized controlled trials are needed to gain insight into the effectiveness of e-cigarettes for smoking cessation.

### Information Need on e-Cigarettes

In line with this ongoing debate, e-cigarette users, smokers, and nonusers reported that they have unanswered questions regarding e-cigarettes [16]. They raised questions about the harmfulness of e-cigarettes, especially compared to cigarette smoking, about the long-term health effects of e-cigarette use, and about e-cigarettes as a smoking cessation method. e-Cigarette users also report a lack of knowledge regarding the ingredients of e-cigarettes and its health effects [17]. Furthermore, incorrect risk perceptions regarding e-cigarette use and tobacco smoking are held by smokers. For instance, only half of the smokers believe that the use of e-cigarettes is less harmful than smoking tobacco [18], and fruit or candy flavors in e-cigarettes are perceived as less risky compared to tobacco flavors [19]. Thus, there is an information need regarding e-cigarettes, especially among smokers who may benefit from e-cigarettes as an aid in smoking cessation.

### Decision Making on e-Cigarettes

Owing to the uncertainty surrounding e-cigarettes, it is important that smokers have sufficient knowledge about e-cigarettes when deciding whether to use them. An informed choice is often defined based on relevant knowledge and the congruence between attitudes and conducted behavior [20]. These conceptualizations of informed decision making employ cut-off points in order to dichotomize constructs into positive and negative outcomes (eg, sufficient knowledge or not). These cut-off points are chosen arbitrarily, indicating that there is neither evidence for the choice of these cut-off points nor evidence that there is an underlying dichotomy at all [21]. Furthermore, individuals who score values close to the cut-off points but on opposite sites (eg, on a scale from 1-10, if 5 is considered to be the cut-off point, individuals who score values close to the cut-off point but on opposite sites would then for instance score 4.9 and 5.1) are categorized as being very different, while in reality being quite similar [21]. In this research, we will avoid dichotomizing continuous variables by examining the constructs of decision making separately.

### Research Goal

The goal of this study will be to assess the effect of tailored communication about e-cigarettes in a digital smoking cessation intervention on determinants of decision making, smoking reduction, and smoking cessation. In the context of a tailored eHealth program, smokers will be randomized into 1 of the 2 conditions—either receiving detailed tailored information about e-cigarettes or not. Information provision about e-cigarettes can have differential effects on smoking behavior, including favorable effects (eg, decreased number of tobacco cigarettes smoked, increased number of tobacco-abstinent participants) as well as unfavorable effects (eg, decreased number of tobacco-abstinent participants). Differences between conditions in the number of dual users (ie, people using e-cigarettes and smoking tobacco cigarettes) will be examined as well. Regarding decision making, we hypothesize that participants in the intervention condition will have more knowledge about e-cigarettes directly after the intervention compared to participants in the control condition. We did not formulate a hypothesis for the determinant attitude as neither a more positive nor a more negative attitude is directly associated with improved decision making. Regarding smoking behavior, we hypothesize that participants in the intervention condition will have smoked less tobacco cigarettes (adjusted for baseline measurement) in the past 7 days at the 6-month follow-up compared to participants in the control condition.

## Methods

### Study Design

A randomized controlled trial will be conducted and the results will be reported according to the CONSORT-EHEALTH checklist [22]. Participants will be 1:1 randomized into either the intervention condition or the control condition. Participants in both conditions will receive the same underlying digital smoking cessation intervention. The 2 conditions differ in the provision of information about e-cigarettes. Smokers in the intervention condition will receive detailed tailored information on e-cigarettes whereas smokers in the control condition will not receive that information. Measurements will be conducted at 3 points in time. A baseline questionnaire will be conducted at the start of the intervention. A first follow-up questionnaire will be conducted directly after completion of the intervention (ie, postintervention). A second follow-up questionnaire will be conducted at 6 months from the baseline. All questionnaires will be web-based and self-assessed. Figure 1 shows the study design.

**Figure 1 figure1:**
[figure not shown]
Flowchart of the study design.

### Participants and Recruitment

Inclusion criteria were that participants are at least 18 years old, have sufficient command of the Dutch language, have necessary internet literacy to use the intervention, have smoked tobacco in the past 7 days, and are motivated to quit tobacco smoking within 5 years. Participants were recruited using multiple strategies. A Dutch research agency was consulted in order to recruit smokers from their participant pool. Google Ads were used to recruit people who were searching the Google search engine for terms around smoking cessation. Social media and smoking-related forums were approached to recruit members of those channels. Moreover, flyers were distributed door-to-door in the Maastricht region, the Netherlands. Incentives were provided to participants who took part in the intervention and who answered all the questionnaires (baseline, postintervention, 6-month follow-up). Ten gift vouchers of €25 (US $1=€0.83) were raffled off among all participants who were recruited organically. Participants stemming from the research agency collected points within the system of the research agency, which could be exchanged for gift vouchers or donations. Interested individuals were directed to an external intervention website. Potential participants were informed that they would receive tailored smoking cessation advice during the intervention. The nature of tailoring was explained to clarify that the advice will be based on the answers participants provide to the questions during the intervention. The aim of this study was stated as exploring the opinion of smokers on the intervention. e-Cigarettes were not mentioned in the participant information text. Potential participants were informed about the possibility to withdraw from the study at any time without providing any reason. Participants did not need to register on the intervention website in order to limit the participation burden. After giving web-based informed consent, the inclusion criteria were verified by a short questionnaire. The intervention would take about 20 minutes (including the baseline and postintervention questionnaire). Answering the 6-month follow-up questionnaire will take about 3 minutes.

### Sample Size Calculation

The sample size was calculated using the ufs package [23] in R. Acknowledging that the accurate estimation of effect sizes is more important than relying on *P* values, we based our sample size calculation on accuracy in parameter estimation for Cohen *d* [24]. Unfortunately, we cannot infer the effect size from earlier research since we are not aware of any prior studies assessing the influence of providing information about e-cigarettes in a digital intervention on decision making and smoking cessation. Thus, we assumed a small effect size as it is usually found in digital health research on smoking cessation interventions [25]. Taking into account the small effect size of Cohen *d* of 0.2, a margin of error (half-width) of 0.15, and a confidence level of 95%, a total sample size of 687 participants is required.

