### Analyses

The focus of all the analyses will be on the effect size accompanied by the confidence interval [41]. Multiple imputations will be conducted to account for the missing observations at 6-month follow-ups. Sensitivity analyses will be conducted for complete cases and intention-to-treat [42]. The primary outcome (number of tobacco cigarettes smoked in past 7 days) will be tested by analysis of covariance [43,44]. The dependent variable will be the number of tobacco cigarettes smoked weekly at the 6-month follow-up. The number of tobacco cigarettes smoked weekly at baseline will be included as the covariate. The independent variable will be the condition. The average number of tobacco cigarettes smoked per day will be tested similarly. Logistic regression analyses will be performed to assess the effect of the intervention condition and control condition on 7-day point prevalence tobacco abstinence and 7-day point prevalence e-cigarette abstinence. Analyses of variance will be performed to test for differences in the determinants of decision making (knowledge and attitude on e-cigarettes) between conditions. Addiction level will be included as a covariate in additional sensitivity analyses. Previous research suggests that the addiction level needs to be considered when assessing the effectiveness of e-cigarettes for smoking reduction and cessation [45]. The open questions will be analyzed per question. Codes for recurrent themes will be created and reported in a table with example quotes and the number of times a theme was addressed.

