## Results

The study is registered in the Netherlands Trial Register [46]. Ethical approval was granted by the Ethics Review Committee Health, Medicine and Life Sciences (FHML-REC) at Maastricht University (FHML-REC/2019/072). This project is supported by a research grant of the National Institute for Public Health and the Environment (Rijksinstituut voor Volksgezondheid en Milieu). Recruitment began in March 2020 and was completed by July 2020. We enrolled 492 smokers in this study. The results are expected to be published in June 2021.

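### 687 participants were required for a half-width of 0.15, but recruitment closed at 492 and the article neither notes the shortfall nor restates the precision

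*Protocol article*

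**What the plan says.** The Sample Size Calculation section of the protocol article says "we based our sample size calculation on accuracy in parameter estimation" for Cohen d and sets no power target. Its effect-size input is "Taking into account the small effect size of Cohen *d* of 0.2", and the sentence goes on to give "a margin of error (half-width) of 0.15, and a confidence level of 95%, a total sample size of 687 participants is required". No dropout rate or inflation is mentioned.

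The Abstract and the Results section both report that recruitment ran from March 2020 and was completed by July 2020. The Results section states: "We enrolled 492 smokers in this study".

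The Analyses section puts the emphasis of every analysis on the effect size and its confidence interval. It expects incomplete follow-up: "Multiple imputations will be conducted to account for the missing observations at 6-month follow-ups". The primary outcome, cigarettes smoked in the past 7 days at 6 months, is analysed by ANCOVA with baseline consumption as covariate. Knowledge and attitude, measured directly after the intervention, are compared by analysis of variance.

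**The concern.** The article prints a required size and a smaller final enrolment, and nothing connects them. There is no acknowledgement of the gap of 195 participants, no revised margin of error, and no argument that 492 is enough.

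This matters more here than in a trial designed on power. Precision is the only justification given for the size, so the half-width of 0.15 is the one design property the reader is offered. A reader who carries that figure forward to the results will expect a narrower interval than the enrolment supports by the plan's own calculation, even before any participant is lost.

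**Working it through.** **Inputs from the article.** d = 0.2, half-width w = 0.15, 95% confidence (z = 1.96), 1:1 allocation, 687 required, 492 enrolled. **Not in the article, so assumed and shown as a range:** 6-month retention, and the correlation r between baseline and 6-month consumption.

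**Step 1: reproduce 687.** With equal arms, the large-sample half-width for an unadjusted d is

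w = z × √[(4 + d²/2) / N], so N = (z/w)² × (4 + d²/2).

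N = (1.96/0.15)² × (4 + 0.02) = 686.3 with unrounded z, rounded up to 687. A check with the noncentral-t interval gives 0.1500 at N = 686 (just above the limit) and 0.1499 at N = 687. The figure is therefore right. Because it reproduces exactly without inflation, it is a number analysed.

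**Step 2: compare with enrolment.** 492/687 = 0.716, a shortfall of 195 (28%).

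**Step 3: the same formula at 492.** w = 1.96 × √(4.02/492) = 0.177, which is 18% wider than 0.15 (0.177/0.15 = 1.18). At d = 0.2 the interval is about 0.02 to 0.38. This step needs no assumption beyond the plan's own.

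**Step 4: allow for loss and for ANCOVA.** For the baseline-adjusted difference, standardised on the unadjusted SD, the half-width is approximately the unadjusted one multiplied by √(1 − r²): 0.866 at r = 0.5 and 0.714 at r = 0.7.

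| Retention (assumed) | Analysed | Unadjusted | ANCOVA, r = 0.5 | ANCOVA, r = 0.7 |
|---|---|---|---|---|
| 100% | 492 | 0.177 | 0.153 | 0.127 |
| 80% | 394 | 0.198 | 0.171 | 0.141 |
| 70% | 344 | 0.212 | 0.183 | 0.151 |
| 60% | 295 | 0.229 | 0.198 | 0.163 |
| 50% | 246 | 0.251 | 0.217 | 0.179 |

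(The entry 0.127 becomes 0.126 if the small d² term is dropped.)

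**Step 5: correlation needed to reach 0.15.** r = √[1 − (0.15/w)²], with w the unadjusted value. This gives 0.53 with no loss, 0.65 at 80% retention and 0.71 at 70%.

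**Step 6: when the interval at d = 0.2 reaches zero.** This happens when the half-width equals 0.2, that is at N = (1.96/0.2)² × 4.02 = 386 unadjusted. 386/492 = 0.785, so about 22% loss. At r = 0.5, N = 0.75 × 386 = 290, so about 41% loss. At r = 0.7, N = 0.51 × 386 = 197, so about 60% loss.

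**The case against.** The best defence has four parts.

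- **The article makes no false claim.** It says what size is needed for 0.15, does not say that 0.15 was achieved, and reports 492 openly. This stands: the sum is correct and the defect is a missing reconciliation. A reader might infer that 687 is an arithmetic error, but it reproduces exactly.
- **The primary analysis is ANCOVA, which can recover precision.** This stands in part. At r of 0.53 or more with no loss, or 0.65 or more at 80% retention, the half-width is 0.15 or less. But the article states no correlation and does not make this argument. Nor does the gain extend to knowledge and attitude, which are measured only after the intervention and compared without baseline adjustment.
- **An attrition allowance may sit in a fuller protocol.** Fair, and with enrolment already below the uninflated figure the allowance is secondary. It cannot explain the gap, because 687 contains no inflation that could absorb a shortfall. Nor does multiple imputation generally restore the information lost with missing outcomes.
- **The achieved interval will be reported anyway and will supersede any planned one.** True. That limits the harm to how readers understand the design beforehand; it does not make the printed figures agree.

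**Conclusion.** The point holds as a failure to reconcile two figures in the same article. The size and precision on which the design rests were not delivered as calculated: 492 against 687, and by the plan's own unadjusted method 0.177 instead of 0.15 before any loss. That much rests only on the article's numbers. The wider values, up to 0.251 at 50% retention, depend on assumed retention.

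Two stronger readings are tempting but unsupported. One is that the trial certainly misses 0.15. For the primary ANCOVA this depends on r and retention, neither of which is given; with r = 0.7 and retention above about 71% (0.51 × 686.3 = 350 analysed, out of 492) it would be met. The other is that an interval around d = 0.2 will include zero. That happens at about 22% loss for an unadjusted d, but only at about 41% loss if r = 0.5.

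No endpoint, analysis or conduct of the trial is affected. This is a correction of disclosure.

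**What to change.** Leave the a priori calculation in the Sample Size Calculation section as it is. Add beside it that:

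- 687 was a target for participants analysed, without allowance for loss, and recruitment closed at 492;
- for outcomes compared without baseline adjustment (knowledge and attitude), the expected half-width at d = 0.2 is at least 0.177;
- for the primary ANCOVA, the expected half-width is a range over stated values of r and 6-month retention, both labelled as assumptions, in the manner of the table above.

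No further enrolment and no change of analysis is needed. The cost is a few sentences and a stated precision that looks less favourable than 0.15.

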### Intervention

The intervention will be a digital computer-tailored smoking cessation intervention that will be partly based on an earlier developed intervention at Maastricht University [26-28]. Compared to generic information, computer-tailored interventions provide highly individualized information that is tailored to the motivational and behavioral characteristics of the recipient [29]. According to the elaboration likelihood model, information that is perceived as personally relevant is expected to lead to more in-depth processing and, in turn, to more sustained attitudinal and behavioral changes [30]. The computer-tailored intervention will be based on the I-Change model [31,32], a comprehensive model that integrates various social-cognitive theories (see Figure 2). During the intervention, participants in both conditions will receive tailored advice on the pros and cons of quitting smoking (ie, attitude), social influence, preparatory plans, self-efficacy, and coping plans concerning smoking cessation. Participants will be able to decide based on their own interests and needs on which determinants of smoking cessation they would like to receive tailored advice. The information for the tailoring process is gathered by means of questionnaires that the recipient has to fill in during the intervention. Subsequently, a computerized process, employing if-then rules, selects appropriate feedback messages from a pool of all messages based on the answers that the recipient has given in the questionnaires [29,33].

The items of the questionnaires are based on previous research [27,28] ([name] and [name], unpublished data, 2021) and are reported in Multimedia Appendix 1. The pros and cons of quitting smoking (eg, “If I stop smoking, my physical fitness will improve”) will be assessed by 16 items. Social influence will consist of 2 components with 2 items each: social modeling (eg, “Does your partner smoke?”) and social support (eg, “Does your partner support you when you decide to quit smoking?”). Figure 3 illustrates an example of tailored advice for social support. Preparatory plans (eg, “I am planning to stop smoking completely without cutting down on cigarettes first”) will be assessed by 5 items. Self-efficacy (eg, “I find it difficult not to smoke if I am stressed”) will be assessed by 11 items. Coping plans (eg, “I have made clear plans to make sure that I will not smoke if I am stressed”) will be assessed by 11 items, reflecting the same situations as assessed for self-efficacy. After answering and receiving information on the determinants of smoking cessation, participants in both conditions will be able to indicate about which 6 clusters of smoking cessation methods they want to receive information (face-to-face counselling, eHealth interventions, telephone counselling, group-based programs, nicotine replacement therapy, and prescription medication).

All advices concerning the pros and cons of quitting smoking, social influence, preparatory plans, self-efficacy, and coping plans will be presented in the form of spoken animations with little on-screen text in order to increase user experience and user engagement [34] ([name] and [name], unpublished data, 2021). A screenshot of an example of a webpage of the intervention with an animation is shown in Figure 4. All texts will be written in simple language and no hyperlinks to other resources will be presented. The website will be developed employing responsive web design and will thus be accessible on all common devices (eg, computer, smartphone) with all types of screen sizes. A second screenshot of a typical webpage presenting 2 questions of the tailoring process is shown in Figure 5.

